### Procedures and techniques

Guidance, insertion and removal of subdermal implants, as well as prescription of other contraceptive methods, electrical bioimpedance and outpatient follow-up will be performed by the researchers. A specialist in Gynecological and Obstetric Ultrasound will perform the ultrasound scans. Subdermal implant placement will follow the manufacture technique [26]. The implant will be inserted with the patient in the supine position, with the medial aspect of the upper arm exposed, the left arm when right-handed, or the right arm when left-handed, approximately 6 to 8 cm above the elbow crease, in the medial bicipital groove. Using an adequate aseptic technique, local anesthetic (2 ml of 1% lidocaine) will be applied, and the implant placed using its own application device in the subdermal connective tissue. After insertion, palpation will confirm its position. In situations where it is not possible to palpate the implant or should there be doubts regarding adequate positioning, an ultrasound scan will be performed for confirmation. Following insertion, occlusive dressings will be applied, and the User Card filled-out and given to the patient. Electric bioimpedance will be performed using bioelectrical impedance, with a single frequency unit (50 kHz), Quantum II Bia Analyzer® brand (Q-JL Systems, Michigan, USA). For this test, the patient will remain in the supine position with the electrodes placed at the following anatomical points: near the metacarpal-phalangeal and the metatarsal-phalangeal joints (current-emitting electrodes); between the distal prominences of the radius and ulna; and between the medial and lateral malleolus of the ankle (voltage sensing electrodes). This method can evaluate percentages of total body fat, fat free mass, dry lean mass, total body water and intracellular water. Ultrasound scans will be performed in the Diagnostic Imaging Sector of the Women’s Hospital using a Voluson 730 Expert device, via transvaginal, endocavitary probe, transvaginal preset, 6.5 MHz frequency, mode B, with focus, gain and depth adjusted. The average time of each US scan will be 15 min, with evaluation of the following parameters: uterine volume, endometrial appearance and thickness, ovarian volume and characteristics, and the presence of corpus luteum or other cysts. All images will be saved on the machine used, as well as an external hard drive.

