## Methods/design

### Study type

A non-randomized and open-label trial.

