### Follow-up

All participant women will be schedule to return to postpartum visit up at 40–60 days, and again at 6 and 12 months post-enrollment. Patient satisfaction, contraceptive effectiveness, rates and reasons of discontinuation and continuation rate, as well as, body composition will be evaluated. Transvaginal ultrasound and electric bio impedance tests will be performed at all follow-up appointments. Non-implant acceptors will start follow-up at the 40–60 day after childbearing. Efficacy, characteristics, and contraindications will be based on the WHO criteria [25]. Women who do not attend the schedule follow-up visits and those who we were unable to contact after three telephone call will be consider lost-to-follow-up (LFU).

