### Sample size

The sample size was calculated based on a prevalence of acceptance of the ENG-implant, based on the satisfaction of teenagers users with the implant [27]. A significance level of 5% and a sampling error (absolute) for the prevalence of 10% were assumed (expected prevalence between 50 and 70%). The formula is based on a binomial distribution (satisfied or not satisfied) n = Z21-a/2 p(1-p) / e2, since e = sampling error of prevalence, p = estimated prevalence (based on literature), a = significance level and Z is the value of normal distribution. The sample size was calculated in *n* = 92,2 and rounded to 100 to contemplate casual lost in the sample. We expected obtaining an estimate of between 50 and 70 teenagers who will accept the method, according to the prevalence and sample error assumed. After collecting the data, the groups will be compared for the dependent variables and the power of the test will be calculated for user satisfaction, method effectiveness, side-effects, body composition, and ultrasound evaluation. The expected flowchart from the study is in Fig. 1.

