## Discussion

Our expectation is that almost 60% of the adolescents after childbearing at our hospital will choose the ENG-implant as contraceptive method due to the higher contraceptive efficacy when compared to non-LARC methods and few side-effects mainly abnormal uterine bleeding. Breakthrown or unscheduled bleeding after ENG-implant placement is the main reason for early discontinuation; however, we expected that in this particular group of users, due to the physiological bleeding after childbearing, this side-effect could be avoided, they will be satisfy and continuation rate could be high than when placement of ENG-implant occurs at interval period.

In addition, it is unlikely that body composition will be affected with the use of the ENG-implant, because it was described that the weigh gain is almost one kg/year after implant placement, with most patients likely to present normal pelvic characteristics during ultrasound scans.

The large number of UP among Brazilian adolescents and young women is one of the main sexual and reproductive health public problem. One of the consequences is the high cost for the national health service of approximately US$ one billion per year and childbearing at adolescent age contribute significantly to this burden [29]. According to data from the Brazilian Ministry of Health, approximately 20% of all pregnant women are teenagers and, ~ 60% are UP. Therefore, we consider that our study could be a demonstration one to provide reliable data on one strategy about how to reduce these indices.

LARC methods, including the ENG-implant are the first option to reduce UP in teenagers [30]. However, there are few studies in the literature that assess its use in this specific population.

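### No provision keeps the ultrasound specialist unaware of the woman's method, although judged scan findings are compared between the groups

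*Protocol article*

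**What the plan says.** Under Study type the design is given as "A non-randomized and open-label trial", and no section makes an exception to open-label status for any role.

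Procedures and techniques divides the work. Counselling, insertion and removal fall to the researchers, and "electrical bioimpedance and outpatient follow-up will be performed by the researchers". The scans are assigned separately: "A specialist in Gynecological and Obstetric Ultrasound will perform the ultrasound scans". That section gives the device, probe, frequency and scan duration, and lists the parameters: "uterine volume, endometrial appearance and thickness, ovarian volume and characteristics, and the presence of corpus luteum or other cysts". It adds that "All images will be saved on the machine used, as well as an external hard drive". It does not say whether the specialist is told which method the woman uses.

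Under Follow-up, "Transvaginal ultrasound and electric bio impedance tests will be performed at all follow-up appointments". The Abstract and the aims at the end of the Background name pelvic ultrasound characteristics among the outcomes examined in both groups. Under Sample size, after a comparison of the groups on the dependent variables, "the power of the test will be calculated for user satisfaction, method effectiveness, side-effects, body composition, and ultrasound evaluation". In the Discussion, the sentence on implant use ends by anticipating the result, "with most patients likely to present normal pelvic characteristics during ultrasound scans".

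**The concern.** Three features come together. Some of the listed parameters are read by judgement, the reader has no stated masking, and the findings enter a between-group test. The authors also publish an expectation about what the scans will show. If the reader knows the method, judged findings could be recorded more or less readily in one group. The chi-square or Fisher test named under Statistical analysis cannot separate such a shift from a real difference.

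The open-label label follows from women choosing their own method. It does not require the person reading the scans to know that choice. At stake is the credibility of a secondary comparison on ultrasound findings. The sample size rests on acceptance of the implant, which does not depend on who reads the scans.

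**Working it through.** **1. Which parameters are exposed.**

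| Measured, less exposed | Judged, more exposed |
|---|---|
| Uterine volume | Endometrial appearance |
| Endometrial thickness | Ovarian characteristics |
| Ovarian volume | Corpus luteum or other cysts |

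**2. Whether masking is feasible.** The specialist is named separately from the researchers who insert and follow up, and scans take place in the imaging sector. The implant lies in the upper arm, outside the field of a transvaginal scan. Statistical analysis already gives each participant an identification number. Images are stored, so a coded re-reading is also possible.

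**3. The plan's own figure.** The article gives no rate, standard deviation or effect size for ultrasound. Its only relevant figure is the total sample size: n = z² p(1 − p)/e² with z = 1.96, p = 0.60 and e = 0.10, giving 3.8415 × 0.24/0.01 = 92.2. This agrees with the stated 92.2, rounded up to 100. With 50 to 70 women expected to accept, the split runs from 50/50 to 70/30, with 60/40 in the middle. Masking the reader changes none of this.

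**4. Illustration of size.** Assumptions, not from the documents: one yes/no judged finding, a true rate of 15% in both groups, and a reading shift in the implant group only. The rejection probability is the sum, over all counts a of 60 and b of 40, of Bin(a; 60, 0.15 + d) × Bin(b; 40, 0.15) wherever the two-sided 5% test is significant. The test is chi-square, or Fisher when any expected count is below 5. In a 2×2 table, one small cell of four is the plan's 25% threshold.

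| Shift d in implant group | More findings | Fewer findings |
|---|---|---|
| 0 points | 0.048 | 0.048 |
| 5 points | 0.088 | 0.107 |
| 10 points | 0.215 | 0.333 |

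An upward shift of 15 points gives 0.406. A downward shift of 15 points would erase every finding in the implant group (15% − 15% = 0), so it is not a useful case.

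Direction matters. The expectation in the Discussion, that scans will look normal, points to the fewer-findings column if it acts on implant users.

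**5. Sensitivity.** For a 10-point upward shift at a 15% true rate, the result is 0.244 at 50/50 and 0.175 at 70/30. With true rates of 10%, 20% and 30% at 60/40, and chi-square throughout, a 10-point upward shift gives 0.247, 0.192 and 0.174.

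**The case against.** The strongest reply is that the article does not say the specialist is told the method. A reader might infer from the open-label label that the specialist is unmasked. The documents do not support that: open-label describes the trial, not what a scan request carries, and a condensed article may leave such detail to the full protocol. This stands, and it limits the point to the absence of any stated provision. It does not dispose of the point, because the article describes the scan procedure closely and the only masking status it states is open-label.

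A reader might also infer that full masking is available at no cost. That does not hold either:

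- The comparison methods are not listed, and intrauterine methods are not excluded. Such a device could be recognised on the scan, and only in the comparison group.
- Procedures and techniques provides for an ultrasound scan when an implant cannot be palpated or its position is in doubt. If the same specialist does it, that woman's method is known.
- The woman is awake and may mention her method, and ovarian or endometrial appearance may hint at it.

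Self-selection also confounds the scan comparison even with a perfectly masked reader. That is correct, and it is the larger problem. But reading bias is a separate source of error that adjustment for patient characteristics would not remove.

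Finally, nothing in the documents supports a reading shift of any particular size, and the stated expectation is the authors' general one, not evidence about the specialist. Both are true, so the figures are illustrations only. The stored images are a partial safeguard, but the article plans no coded reading of them.

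**Conclusion.** The point holds in a limited form, as an optional improvement and not an error. The plan as written contains no safeguard against knowledge of the method influencing judged ultrasound findings that are compared between groups. The documents do not show that the specialist is in fact told the method, nor that any reading bias will occur.

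Under the stated assumptions (60 versus 40 women, true rate 15%, shift in the implant group only), false significance rises from about 5% to about 9–11% with a 5-point shift and about 22–33% with a 10-point shift, depending on direction. Measured volumes and thickness are less affected. Acceptance, and with it the sample size, is not affected. Masking would remove one source of bias and leave the confounding from self-selection in place.

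**What to change.** In Procedures and techniques, add that:

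- scan requests carry only the study number and visit;
- the specialist is not told the method;
- the judged parameters are recorded before any disclosure;
- the operator notes whether the method became known, and how.

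If the full protocol already provides this, one line in the article saying so is enough. Where the method became known, the saved images allow a coded second reading of the judged items, though that takes extra reader time.

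The cost of the main change is a revised request form and one extra item on the scan record, with no additional staff, visits or scans. The downside is incomplete masking for intrauterine users, for women who had an implant-localisation scan by the same specialist, and for women who reveal their method. Since this may fall unevenly across the groups, report how often the method became known in each group, and identify intrauterine users separately.

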### Sample size

The sample size was calculated based on a prevalence of acceptance of the ENG-implant, based on the satisfaction of teenagers users with the implant [27]. A significance level of 5% and a sampling error (absolute) for the prevalence of 10% were assumed (expected prevalence between 50 and 70%). The formula is based on a binomial distribution (satisfied or not satisfied) n = Z21-a/2 p(1-p) / e2, since e = sampling error of prevalence, p = estimated prevalence (based on literature), a = significance level and Z is the value of normal distribution. The sample size was calculated in *n* = 92,2 and rounded to 100 to contemplate casual lost in the sample. We expected obtaining an estimate of between 50 and 70 teenagers who will accept the method, according to the prevalence and sample error assumed. After collecting the data, the groups will be compared for the dependent variables and the power of the test will be calculated for user satisfaction, method effectiveness, side-effects, body composition, and ultrasound evaluation. The expected flowchart from the study is in Fig. 1.

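### Power of the group comparisons is to be calculated after data collection with no target difference stated; confidence intervals and detectable differences fixed beforehand should replace it

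*Protocol article*

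**What the plan says.** The Sample size section derives the number of women from a one-sample formula for a proportion: "A significance level of 5% and a sampling error (absolute) for the prevalence of 10% were assumed", with "expected prevalence between 50 and 70" per cent. The result is "92,2 and rounded to 100 to contemplate casual lost in the sample". The formula has no power term and no second group.

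The between-group comparisons enter in one later sentence of the same section: "After collecting the data, the groups will be compared for the dependent variables and the power of the test will be calculated". The outcomes it lists are user satisfaction, method effectiveness, side-effects, body composition and ultrasound. The article gives no difference of interest and no standard deviation for any of the five.

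The Statistical analysis section plans chi-square or Fisher tests for qualitative variables and t or Mann-Whitney tests for quantitative ones, all at the 5% level. The Discussion states a prior view on one of the five outcomes: "it is unlikely that body composition will be affected with the use of the ENG-implant".

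**The concern.** Comparing the two groups is a declared aim in the Abstract and the Background, so a reader will want to know what about 100 self-selected women can reveal. The plan answers with a power figure produced once the results are known. If that power is taken at the observed difference, it says almost nothing that the p-value has not already said. A non-significant t-test or two-by-two comparison would then carry a low power figure whether its confidence interval was wide or narrow.

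The risk is sharpest for body composition. No effect is expected there, yet the only planned analysis is a test for a difference. A non-significant test with a power figure attached does not show that body composition is unaffected, and it does not show how large an effect remains possible.

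**Working it through.** **1. The plan's own figure.** Inputs from the Sample size section: two-sided alpha 0.05 (z = 1.96) and absolute error e = 0.10. The prevalence p is 0.60, the midpoint of the stated range and the expectation in the Discussion.

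n = z² p(1−p)/e² = 1.96² × 0.60 × 0.40 / 0.01 = 92.2. This reproduces the stated value. At p = 0.50 the formula gives 96.0 and at p = 0.70 it gives 80.7, so 100 covers the whole range. The sample size is correct for its own purpose.

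**2. Power at the observed effect.** For a z-type test with two-sided p-value p, let z_obs be the normal quantile at 1 − p/2. Then

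observed power = Φ(z_obs − 1.96) + Φ(−z_obs − 1.96).

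| p-value | z_obs | Observed power |
|---|---|---|
| 0.05 | 1.960 | 0.50 |
| 0.20 | 1.282 | 0.25 |
| 0.50 | 0.674 | 0.10 |

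The formula contains neither the sample size nor the SD. A t-test with 98 degrees of freedom gives the same values to two decimals.

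**3. Why this cannot separate the two explanations.** Take p = 0.20 with groups of 60 and 40. The standard error is √(1/60 + 1/40) = 0.204 SD, so the observed difference is 1.282 × 0.204 = 0.26 SD, and the 95% interval is 0.26 ± 0.40, or −0.14 to 0.66 SD. Now take p = 0.20 in a hypothetical study ten times larger. The standard error is 0.204/√10 = 0.0645, the difference is 0.083 SD and the interval is −0.04 to 0.21 SD. Observed power is 25% in both. The intervals differ greatly in what they rule out; the power figure does not.

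**4. Where the relation is looser.** For a chi-square test with several degrees of freedom, setting the noncentrality to the observed statistic gives power at p = 0.05 of 0.58 (2 df), 0.64 (3 df) and 0.69 (4 df). For a given number of degrees of freedom it is still a function of the p-value, but not the one in step 2. For Fisher's exact test the relation is approximate. At 60/40, 1/60 versus 4/40 gives p = 0.154 and power 0.37, while 21/60 versus 20/40 gives p = 0.151 and power 0.27.

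**5. What can be stated beforehand.** The Sample size section expects 50 to 70 acceptors among 100, hence 50 to 30 comparators. The 80% power is an assumption, because the article gives none. Half-width = 1.96 × √(1/n₁ + 1/n₂). The detectable difference is for the two-sided t-test at 5%.

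| Split | √(1/n₁ + 1/n₂) | 95% CI half-width (SD) | Detectable at 80% power (SD) |
|---|---|---|---|
| 50/50 | 0.200 | 0.39 | 0.57 |
| 60/40 | 0.204 | 0.40 | 0.58 |
| 70/30 | 0.218 | 0.43 | 0.62 |
| 55/37 | 0.213 | 0.42 | 0.60 |

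The last row uses 92 women, the number before the allowance for losses, split 60:40 (92 × 0.60 ≈ 55).

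For proportions, also at 80% power and with assumed comparator rates, the detectable difference over these splits of 100 is about 27 to 28 points from 50%, 22 to 23 points from 70%, and 17 to 18 points from 80%.

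**The case against.** The article does not say at which effect the power will be calculated. Power at a chosen difference, using the achieved group sizes and SDs, would not restate the p-value, and the achieved split is unknown in advance because the women choose their own group. This stands as a limit: the restatement argument is conditional. It does not rescue the sentence, because no such difference appears in the article, and one chosen after the results are seen would itself be open to choice.

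Three stronger readings are tempting and not supported:

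- A reader might infer that every non-significant result must show observed power of 50% or less. That holds for z-type and one-degree-of-freedom tests. The planned chi-square tests may have more than two categories, and Fisher's test is also planned, so it is not universal (step 4).
- A reader might infer that the plan expects no group difference on ultrasound. The Discussion says only that most women will probably have normal scans, which describes frequency and not equality of the groups.
- A reader might infer that the investigators intend to conclude no effect from a non-significant test. The Discussion states an expectation and not a decision rule. Misreading is a plausible risk but not part of the plan.

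It is also fair to say that the sample size was set for acceptance, where it is adequate, and that the comparisons are additional to that.

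**Conclusion.** The point holds in a conditional form. The plan commits to calculating power after data collection for five comparative outcomes and gives no target difference for any of them. On the natural reading, power at the observed effect, the figure is essentially a re-expression of the p-value for t-type and one-degree-of-freedom tests. It therefore cannot tell an absent difference from an imprecise estimate.

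The informative quantities are available now. Over the expected splits of 100 women, the 95% interval half-width for a mean difference is 0.39 to 0.43 SD, and the detectable difference is 0.57 to 0.62 SD. Both are slightly worse with losses. They rest on an assumed 80% power, a 5% two-sided test, equal SDs in the two groups and, for the 100, complete follow-up.

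The acceptance estimate and its sample size are not affected. The weakness lies in how the comparative results would be interpreted, above all for body composition. It should be corrected, but it does not undermine the study.

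**What to change.** 1. Delete the sentence on calculating power after data collection.
2. State in its place what the expected split can show for each comparative outcome: the 95% interval half-width and the difference detectable at a named power, at 60/40 and over 50/50 to 70/30, with an allowance for losses.
3. Report every between-group contrast as an estimate with a 95% confidence interval.
4. For body composition, either name beforehand the largest difference regarded as unimportant and conclude no effect only if the whole interval lies within it, or call the comparison exploratory.

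The cost is wording in the protocol or analysis plan. Sample size, visits, measurements and treatment stay as they are.

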**Fig. 1 Fig1:**
[figure not shown]
Expected Flowchart

### Statistical analysis

The data will be recorded in a data collection sheet prepared for this study. The encrypted data will be stored anonymously in a excel database, after manual review and double typing for descriptive statistical analysis (mean, standard deviation, absolute and relative frequency distribution). The association between independent and dependent variables will be performed using the X^2^test (for qualitative variables) or Fisher’s exact test (when 25% or more of the expected values ​​are less than 5) and through the Student’s *t* test (or the Mann-Whitney test if the data do not present normal distribution, as well as logarithmic, inverse and quadratic transformations of the same). Open questions will be categorized for application of statistical analyzes as well as qualitative variables. Additionally, we will estimated the couple year protection (CYP) which is an indicator of the number of pregnancies averted in each of the groups under evaluation. The level of significance adopted for the statistical tests will be 5%. For statistical analysis, the program Statistical Analysis System (SAS), version 9.4 will be used. Other procedures will be adopted for quality control. Each patient will have an identification number so as not to permit confusion of data, the completed forms will be reviewed and the data put on to the database by two different typists in order to avoid losses and typing errors. All material used for data collection will be stored by the researcher for five years, remaining confidential. This article has followed the SPIRIT guidelines for its elaboration [28].

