Otherwise, placement of the ENG-implant is considered safe during breastfeeding and do not presents maternal, neonatal or postpartum risks [11, 13–16]. with no risk of expulsion as occurred with IUC [19].

Also, teenagers presented a high adherence rate when using LARC, with rates of 84 and 74% for the subdermal implant and IUD, respectively [20]. Abnormal uterine bleeding is cited as the main reason for withdrawal of the method [21].

However, a study with women who opted for insertion of the ENG- implant during the immediate postpartum period and followed-up over 3 years, showed that teenagers, who represented 28.2% of the sample, had high continuation rate (94.5%) [22].

The repetition of an UP among teenagers is associated with a low level of schooling, drug addiction and incorrect use of contraceptives among other causes [23]. In this population, the incidence of a new pregnancy within 2 years after the first one was 35%; however, with placement of any LARC at the immediate postpartum period, the rate decreased by 88.2% when compared to non-LARC methods [24].

The aim of our study is to evaluate acceptability, contraceptive efficacy, discontinuation rate by reasons and continuation rates among adolescents who either accept the ENG-implant versus non-acceptors at the immediate postpartum period and follow-up up to one year after placement. In addition, information regarding the relationship between implant use and body composition, pelvic ultrasound characteristics and user satisfaction will be analyzed in both groups.

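### One-year continuation, discontinuation by reason and pregnancy are left to percentages and chi-square or Fisher tests that cannot use partly observed women, so the result depends on an unstated denominator

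*Protocol article*

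**What the plan says.** The aim at the end of the Background covers acceptability, efficacy and "discontinuation rate by reasons and continuation rates among adolescents who either accept the ENG-implant versus non-acceptors", followed up to one year after placement. The Follow-up section repeats "rates and reasons of discontinuation and continuation rate" among the outcomes, sets visits at 40–60 days and at 6 and 12 months, and defines when a woman counts as lost to follow-up.

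The Statistical analysis section describes the data by "descriptive statistical analysis (mean, standard deviation, absolute and relative frequency distribution". It says associations will be "performed using the X^2^test (for qualitative variables"), with Fisher's exact test when expected counts are small. The t or Mann-Whitney test covers measured variables, and couple year protection is added. "The level of significance adopted for the statistical tests will be 5" per cent. The article names no life-table, Kaplan-Meier, log-rank, cumulative-incidence or woman-years method, and gives no rule for placing lost women in a denominator.

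The only allowance for loss is in the Sample size section, where 92.2 is "rounded to 100 to contemplate casual lost in the sample".

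**The concern.** Continuation over a year is a time-to-event outcome. A woman last seen at 6 months and still using her method contributes half a year of information, but a two-by-two table has no cell for her. She must be counted as stopped, counted as continuing, or removed. The three choices give three different rates, and the article does not say which applies. The choice could therefore be made after the data are seen.

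Reasons for stopping also compete with one another and with pregnancy, which separate crude percentages do not reflect.

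Unequal loss between the groups is plausible. The implant is placed before discharge, whereas the comparison group must come back at 40–60 days to obtain a method, so the two groups have different reasons to attend. Depending on the rule chosen, a comparison meant to show continuation of the method may partly show retention in the study.

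**Working it through.** **Inputs from the article.** Two-sided 5% level. Absolute error 0.10 ("A significance level of 5% and a sampling error (absolute) for the prevalence of 10% were assumed" in the Sample size section). "expected prevalence between 50 and 70" per cent acceptance, with about 60% expected in the Discussion, hence about 60 implant and 40 comparison women. Implant failure rate 0.4 per 100 women per year (Background).

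**Assumptions.** True 12-month continuation S = 0.84 in both groups. The Background gives 84% as an implant adherence rate without a time horizon, so its use here, and for the comparison group, is hypothetical. Loss per group is not given, so a range is shown. Hazards are constant, and loss is independent of stopping.

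**The plan's own figure.** n = 1.96² × 0.60 × 0.40 / 0.10² = 92.2, which reproduces. Rounding to 100 leaves 7.8 of 100, an implied overall loss of 7.8%. The sample size is not in error on this point.

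**Crude rates under each rule.** With λ = −ln S and μ = −ln(1 − L), where L is the 12-month loss:
- seen to continue, c = S(1 − L)
- seen to stop, d = λ/(λ + μ) × (1 − c)
- lost, 1 − c − d

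For L = 0.30: λ = 0.174 and μ = 0.357, so c = 0.84 × 0.70 = 0.588, d = (0.174/0.531) × 0.412 = 0.135, and 0.277 are lost.

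| Loss | Lost = stopped: c | Lost dropped: c/(c + d) | Lost = continuing: 1 − d |
|---|---|---|---|
| 7.8% | 77% | 83% | 85% |
| 10% | 75.6% | 83.3% | 84.8% |
| 30% | 58.8% | 81.3% | 86.5% |

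With 10% loss in one group and 30% in the other, and no true difference, the apparent gap is 75.6 − 58.8 = 16.8 points under the first rule. It is about 2 points under each of the others (83.3 − 81.3; 86.5 − 84.8).

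**False-positive rate at nominal 5%.** Simulation of 60 versus 40 women with true continuation of 84% in both groups, using chi-square, or Fisher when at least 25% of expected counts are below 5:

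| Loss, implant v comparison | Lost = stopped | Lost dropped | Lost = continuing |
|---|---|---|---|
| 5% v 12% | 12% | 5% | 5% |
| 10% v 20% | 15% | 4% | 4% |
| 10% v 30% | 43% | 5% | 5% |

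The 5% v 12% row averages (60 × 5 + 40 × 12)/100 = 7.8%, the implied allowance. A log-rank test censored at loss rejected in 5.1% of runs at 10% v 30%, and in 4.5% at 10% v 20%.

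**Power when a difference exists.** True continuation 84% v 60%, loss 30% (implant) v 10% (comparison): power is 8% with lost counted as stopped, 62% with lost dropped, 83% with lost counted as continuing, and 75% by log-rank. With loss reversed to 10% v 30%, the figures are 93%, 80%, 61% and 74%. The log-rank figure hardly moves, while the crude tests change with the rule and with the direction of the loss.

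**Pregnancy.** Expected implant failures: 0.004 × 60 = 0.24 in 60 woman-years. If none occurs, the exact Poisson upper limit is −ln(0.025)/60 = 0.0615, or about 6.1 per 100 woman-years.

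**The case against.** The strongest reply is that the article assigns no test to any particular outcome, and that denominators and the handling of lost women are commonly settled in an analysis plan. That lowers the weight of the point but does not remove it. The section is specific enough to state the expected-count rule for Fisher and three data transformations, and it gives one family of tests for yes/no outcomes. Read as written, continuation, discontinuation and pregnancy fall to that family.

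A reader might infer that unequal loss alone will produce a spurious group difference nearly half the time. The documents do not support that. The 43% needs two things the article does not state: that lost women count as stopped, and that loss is 10% v 30%. The Follow-up section gives loss its own category, which fits that rule poorly. The exclusion criteria remove women unable to attend, and the only loss allowance is about 7.8%. If loss is unrelated to outcome, dropping lost women or counting them as continuing holds the error rate near 5%.

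Three further objections stand in part. Censoring also assumes non-informative loss, so Kaplan-Meier does not cure bias from informative loss. With 84% continuation there are about 0.16 × 60 = 9.6 and 0.16 × 40 = 6.4 stops, too few for a curve per reason. The pregnancy interval is mainly a matter of reporting precision: with full follow-up, the exact binomial upper limit for 0 of 60 is 6.0%, close to the Poisson figure.

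**Conclusion.** The point holds in a limited form. The stated methods cannot use women observed for part of the year, and the continuation rate depends on a denominator the article does not fix. Under the assumptions above, the spread across the three rules is 86.5 − 58.8 = 27.7 points at 30% loss and about 8 points (85 − 77) at the loss the sample size implies. Inflation of the false-positive rate arises only when lost women count as stopped: about 43% at 10% v 30% loss and about 12% at 5% v 12%. Under the other two rules the gain from a censored analysis is less dramatic: it uses all observed time and fixes the rule in advance. All loss rates other than the 7.8%, and the common 84%, are assumptions. The change is worth making because it is cheap, not because the planned comparison is bound to mislead.

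**What to change.** In the Statistical analysis section, state the following:

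- Continuation is analysed as time to discontinuation from method start, with the origin defined for each group (implant within 48 h of birth; other methods at 40–60 days), censored at last contact. Report Kaplan-Meier 12-month estimates with 95% confidence intervals and a log-rank comparison. State how 12 months is counted: if enrolment is dated close to the birth, a comparison woman reaches the 12-month visit with only about 365 − 60 = 305 to 365 − 40 = 325 days on her method. A common time that both groups reach should then be named.
- Discontinuation by reason is reported as cumulative incidence for a few grouped main reasons, because events are few, with other reasons and pregnancy as competing events.
- Pregnancies are reported per 100 woman-years with exact Poisson 95% limits.
- A sensitivity analysis counts lost women as stopped, because censoring assumes non-informative loss. It is labelled as an extreme case, given the behaviour shown above.
- Chi-square and Fisher tests are kept for fixed yes/no variables.

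The cost is a few sentences and standard SAS 9.4 procedures, with no change to sample size or visits. Stop dates must be asked at each visit. Removal dates are available for implants, since the researchers remove them. For self-stopped methods the dates will be recalled, or known only to lie between two visits, and this should be acknowledged.
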